#### Primary outcome

2.6.1

The primary outcome will be *insomnia severity*, measured with the Insomnia Severity Index (ISI), which is a reliable and valid instrument, with internal consistency coefficients of *α* = 0.90 in community samples and *α* = 0.91 in clinical samples (Morin et al., 2011). The ISI consists of 7 items with a 5-point Likert scale (0 = not at all, 4 = extremely) and scores range from 0 to 28, with higher scores indicating more severe insomnia. The ISI has been validated for online use (Thorndike et al., 2011). The main endpoint will be at post-test (6 weeks after baseline). Secondary endpoint will be the 18-week follow-up. Participants are treatment remitters if the ISI score at T2 is <10, and treatment responders if there is a reduction in the total ISI score of >8 (Morin et al., 2011).

#### Secondary outcomes

2.6.2

Secondary outcomes will be administered at baseline (T0), 6 weeks (T2), and 18 weeks follow-up (T3).

##### Munich Chronotype Questionnaire (MCTQ)

2.6.2.1

We will assess the 17-item MCTQ, which is a relatively objective self-report questionnaire, since it deals with specific sleep- and wake times. The MCTQ asks for sleep- and wake-times on work/study days and on free days over the past four weeks. Based on this, we can calculate *social jetlag* (the difference in mid-sleep between work/study days and free days), *average weekly sleep duration*, and *average weekly light exposure*, which will be reported as secondary outcomes. We can also determine the *chronotype* (the midpoint between sleep on- and offset on free days corrected for sleep debt accumulated over the workweek), which will be assessed as a moderator (Roenneberg et al., 2003). The MCTQ mid-sleep point shows high correlation with dim light melatonin onset, which is the gold standard for assessing central circadian timing in humans (Kantermann et al., 2015).

#### Patient Health Questionnaire (PHQ-9)

2.6.2.2

*Depressive symptoms* will be measured with the 9-item PHQ-9 (Kroenke et al., 2001), which is a frequently used, reliable and valid measure for severity of depression (Wittkampf et al., 2007). The items are on a scale from 0 to 3 with total scores ranging from 0 to 27. Higher scores indicate higher depression severity.

##### Generalized Anxiety Disorder Scale (GAD-7)

2.6.3.1

*Anxiety symptoms* are measured with the 7-item GAD-7 (Spitzer et al., 2006). The items are on a scale from 0 to 3 with total scores ranging from 0 to 21. Higher scores indicate higher anxiety severity. The GAD-7 is a psychometrically sound measure in university students (Byrd-Bredbenner et al., 2020).

##### Work and Social Adjustment Scale (WSAS)

2.6.3.2

*Daily functioning* will be assessed with the 5-item WSAS, a brief and reliable 5-item questionnaire to assess impairment of functioning (Mundt et al., 2002). Items have a scale from 0 to 8 with total scores ranging from 0 to 40. Higher scores indicate more impairment in functioning. The WSAS shows high internal reliability and sensitivity to treatment effects (Zahra et al., 2014).

##### Mental Health Quality of Life Questionnaire (MHQoL)

2.6.2.5

*Quality of life* will be measured with the 8-item MHQoL, which is a simple and effective measure to assess quality of life (Van Krugten et al., 2021). It has seven dimensions, covering self-image, independence, mood, relationships, daily activities, physical health, and future, as well as a general visual analogue scale. Items are answered on a four-level scale, and scores are ranging from 0 to 21, with higher scores indicating a better quality of life. The MHQoL-VAS visual scale additionally measures general psychological well-being on a scale of 1–10.

##### Academic performance

2.6.2.6

Students will be asked about the grade of their last exam (Grade 1–10), the average grade of the past semester (Grade 1–10), whether they failed any courses in the past semester (Yes/No), and their study progression in the past semester in terms of ECTS achieved (30 ECTS per semester: Yes/No). The grading system is consistent across universities.

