**Objectives:**

We aim to evaluate the effectiveness of a guided online sleep and biological clock self-help intervention in improving sleep, depression symptoms, anxiety symptoms, functioning, academic performance, and quality of life in university students at 6 weeks and 18 weeks.

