### Participants & setting

2.2

The study takes place in a university setting within nine Dutch universities (Leiden University, VU Amsterdam, University of Utrecht, Maastricht University, Erasmus University Rotterdam, Universiteit van Amsterdam, Inholland University of Applied Sciences, Avans University of Applied Sciences, and Rotterdam University of Applied Sciences). These universities belong to the Caring Universities Consortium, the Dutch branch of the World Health Organization College Student Initiative (The World Mental Health Survey Initiative, 2023), who conduct a yearly mental health screening in students and offer free online services to improve student's mental wellbeing.

Students are eligible when they fulfil the following criteria: having self-reported insomnia symptoms of at least subthreshold clinical severity (Insomnia Severity Index-score ≥ 10; ISI) (Morin et al., 2011), aged 16 years or above, affiliated with one of the participating Universities as Bachelor, Master or PhD student, being fluent in English or Dutch. Exclusion criteria are a current risk for suicide. Students are asked about the occurrence of suicidal thoughts in the past 12 months. After positive response, they are asked what the likelihood of acting on the suicidal thoughts is in the coming 12 months. If the likelihood of acting on these thoughts is anything other than “Not likely at all”, they are excluded from the study. The second exclusion criteria are night shifts (not being able to comply with the intervention due to night shifts, meaning work between 2 AM and 6 AM at least once a week). Due to the pragmatic nature of the trial, students using medication or receiving additional psychological treatment will not be excluded as they might still benefit from the intervention, but use of additional treatments will be monitored.

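### Three of the four academic-performance items look back over the past semester, so at the 6-week visit they would mostly re-report results from before randomisation

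*Protocol article*

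**What the plan says.** Section 2.6.2.6 of the Protocol article defines academic performance by four self-reported items:

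- "the grade of their last exam", with no look-back period;
- "the average grade of the past semester";
- "whether they failed any courses in the past semester (Yes/No), and their study progression in the past semester in terms of ECTS achieved", which covers two items. The ECTS item is described as "30 ECTS per semester: Yes/No".

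Three of the four therefore refer to the past semester.

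On timing, section 2.6.2 gives one schedule for the whole group of secondary outcomes: "Secondary outcomes will be administered at baseline (T0), 6 weeks (T2), and 18 weeks follow-up (T3". The abstract's objective covers "functioning, academic performance, and quality of life in university students at 6 weeks and 18 weeks". Section 2.6 makes T2 the primary endpoint. Section 1.1 expects improvement in academic performance but attaches no visit to that expectation. Section 2.2 admits anyone "affiliated with one of the participating Universities as Bachelor, Master or PhD student".

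**The concern.** An outcome can respond to treatment only to the extent that it covers time after randomisation. Other look-back periods respect this. The chronotype questionnaire (section 2.6.2.1), for example, covers four weeks, which fits inside the six weeks to T2. A semester does not fit. At T2 many students would either describe the same completed semester that they described at baseline, or describe a window that lies largely before they entered the trial.

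What is at stake is interpretation. The intervention could have a real academic effect and the three items would still show little difference at 6 weeks. As the objective names 6 weeks for this outcome, that result could be reported as evidence of no academic benefit.

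**Working it through.** **Plan's own figure.** The article gives no calculation for academic performance. Its one computed figure, 48 per group for the ISI, reproduces: 2 × (1.960 + 0.842)² / 0.4² = 98.11, times (1 + 2 × 0.23)/3, gives 47.75, so 48 per group. With 50% drop-out this is 96 per group, 192 in total. The point below does not depend on it.

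**Inputs.** T2 is at 6 weeks and T3 at 18 weeks (section 2.6). Semester length L is not stated. I assume 15 to 26 weeks and show the range.

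**Two readings of the past semester.**

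1. *Last completed semester.* With entry spread evenly over the semester (an assumption), the chance that a semester ends between baseline and week t is min(1, t/L). Everyone else reports the same semester as at baseline.
2. *Rolling window of one semester.* The share of the window lying after randomisation is also min(1, t/L).

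| L (weeks) | T2: 6/L | T2: remainder | T3: min(1, 18/L) |
|---|---|---|---|
| 15 | 40% | 60% | 100% |
| 18 | 33% | 67% | 100% |
| 20 | 30% | 70% | 90% |
| 22 | 27% | 73% | 82% |
| 26 | 23% | 77% | 69% |

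The remainder at T2 is the share of participants repeating their baseline semester (reading 1) or the share of the window before randomisation (reading 2). It exceeds one half whenever 6/L < 0.5, that is, for any semester longer than 12 weeks.

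**What the dilution could do (illustration only).** Borrow d = 0.4 from the ISI calculation. Suppose it appears in full in participants who pass a semester end and not at all in the others. The diluted effect is 0.4 × 6/L:

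- L = 26: 0.4 × 0.231 = 0.09;
- L = 20: 0.4 × 0.30 = 0.12;
- L = 15: 0.4 × 0.40 = 0.16.

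For a two-sample comparison at one time point with 96 per arm, power is 9%, 13% and 20% respectively, against 79% undiluted. With 48 per arm it is 7%, 9% and 12%, against 50%.

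**Limit of T3.** Under reading 1 with L of 18 weeks or more, students who pass a semester end before T3 do so on average 9 weeks after randomisation. Then 9/L, from 50% (L = 18) to 35% (L = 26), of that semester's weeks are post-randomisation. T3 is much better than T2 but not clean.

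**The case against.** Several objections have force.

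- **The outcome is not fixed at zero.** A reader might infer that the whole T2 academic result is null by construction. The documents do not support that. The last-exam grade has no semester window and can change within six weeks. On the figures above, 23 to 40% of participants do pass a semester end by T2. Grades and failures are also decided at exam time, so students with exams inside the six weeks contribute real information.
- **Even entry is an assumption.** Recruitment runs from November 2023 to a planned July 2024 and draws partly on an annual screening survey (section 2.3). Clustered entry could move the shares either way.
- **The schedule is not fully visible.** The sentence in section 2.6.2 is general, and the diary, in the same group, follows its own weeks (1 and 7). Table 2 is not shown. If it omits academic performance at T2, it would conflict with the abstract's objective, and the two would still need to be reconciled.
- **Misclassification of PhD students is not established.** Their eligibility and the Yes/No wording of the ECTS item invite the inference that students without courses are scored as not progressing. But the questionnaire and any not-applicable option are not shown, and the share of PhD students is unknown. Such error would be about equal between arms under randomisation: noise, not bias towards one arm.
- **The list of modelled outcomes in section 2.8.1 omits academic performance.** That omission, and the choice of model for two binary items, are details that an article can leave to the analysis plan. I draw nothing from them.

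What remains is that a semester-long look-back at a 6-week visit is a choice the article itself states, and none of these objections makes the three items informative at T2 for most participants.

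**Conclusion.** The point holds for the three past-semester items at T2. For assumed semesters of 15 to 26 weeks and even entry, about 60 to 77% of participants repeat a pre-randomisation semester, or 60 to 77% of a rolling window precedes randomisation. The comparison is strongly diluted towards no difference, and a null result there is largely uninformative. The direction needs only a semester longer than 12 weeks and entry not concentrated just before semester ends; the exact share depends on both assumptions.

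The point does not extend to the last-exam grade when the exam was sat after randomisation. It concerns one self-reported secondary outcome; the ISI analysis and the sample size are untouched. It is worth correcting because the correction is cheap and prevents a misleading statement about academic benefit.

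**What to change.** 1. Make T3 the analysis time point for the average grade, failed-course and ECTS items, adjusted for the baseline answer. If they are still collected at T2, do not interpret them as an effect of the intervention.
2. Keep the last-exam grade at T2, but only for exams sat since randomisation. This needs a question on when the exam took place. Because sitting an exam is itself a post-randomisation event, report how many in each arm contribute.
3. Analyse the failed-course and ECTS items only in students enrolled in courses, with enrolment taken from baseline so that it cannot depend on arm.
4. Amend the objective so that 6 weeks is not claimed for the past-semester items.

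The past-semester wording should stay as it is at T3. Counting credits since randomisation would not fit a threshold of 30 per semester, and it would make the baseline and T3 answers measure different things.

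The cost is one fewer time point and a somewhat smaller denominator for one secondary outcome. Part of the T3 window may still precede randomisation, which should be stated when the result is reported. With recruitment starting in November 2023, participants already past T2 may lack the exam date.

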##### Sleep & light exposure diary

2.6.2.7

The sleep and light exposure diary will be assessed in the first seven days after baseline measurement (week 1) and in the seven days after the post-test measurement (week 7). The sleep diary is based on the Carney consensus sleep diary and the light exposure items on the Harvard Light Exposure Assessment (Carney et al., 2012; Bajaj et al., 2011). Text adaptations were made in consensus with a group of sleep researchers. Outcomes that will be derived from this diary will be *sleep onset latency* [SOL; number of minutes from lights off to sleep onset], *wake after sleep onset* [WASO; number of minutes awake between sleep onset and final awakening], *early morning awakening* [EMA; number of minutes between final awakening and getting up], *number of awakenings* [NA], *time in bed* [TIB; number of minutes between lights off and getting up], *total sleep time* [TST; TST = TIB – SOL – WASO - EMA], *sleep efficiency* [SE; SE = TST / TIB x 100]. Students also rate their *sleep quality* and how *rested* they feel in the morning [both rated from 0 to 10]. Additionally, *timing and duration of light exposure* and *screen use before bedtime* [Yes/No] will be assessed. Diary items are described in detail in a supplementary file.

#### Other measures

2.6.3

##### Dysfunctional beliefs and attitudes about sleep (DBAS-10)

2.6.2.3

We will measure *dysfunctional beliefs and attitudes about sleep* with the abbreviated DBAS-10 (Edinger and Wohlgemuth, 2001). The 10 items are scored on a scale from 0 (strongly disagree) to 10 (strongly agree). The DBAS-10 has appropriate internal consistency, effectively discriminates normal sleepers from insomnia sufferers, and detects cognitive changes resulting specifically from CBT interventions (Edinger and Wohlgemuth, 2001).

##### Pre-Sleep Arousal Scale (PSAS)

2.6.2.4

We will measure *pre*-*sleep arousal* with the 16-item PSAS. The items are scored on a 5-point Likert Scale, with higher scores reflecting more arousal. The PSAS is a commonly used scale and seems to have appropriate psychometric properties (Jansson-Fröjmark and Norell-Clarke, 2012).

##### Stressful life events

2.6.3.3

Stressful life events can have an impact on sleep and will therefore be examined as a possible covariate (Li et al., 2019). We will ask about whether participants experienced life-threatening or serious accident/ illness, death of someone close, physical/sexual violence or abuse or other incidents, at all time-points.

##### Adverse events

2.6.3.4

Adverse events will be examined at T1, T2, and T3, asking about 1) falling accidents, 2) traffic accidents, or 3) any other accidents related to fatigue or sleepiness, and its consequences. Clinical symptom deterioration will also be reported based on the reliability change index (Jacobson and Truax, 1991).

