#### Mediation and moderation analyses

2.8.2

Mediator and moderator analyses are exploratory and follow the principles by Kraemer et al. (Kraemer et al., 2002). Chronotype will be examined as moderator of the intervention effect on insomnia, by adding the variable to the linear mixed models of insomnia severity as an interaction term (e.g. time x group allocation x moderator). If chronotype will have a significant interactive effect with treatment on the outcome, it is a moderator; with main effect and no interactive effect it is a predictor of response (Kraemer et al., 2002). Additionally, an exploratory investigation of the potential moderating variables will be conducted, including sociodemographic variables and symptom severity, without pre-defined hypotheses, by using the QUINT method (Qualitative Interaction Trees) (Dusseldorp et al., 2016a). The QUINT method identifies three participant subgroups based on baseline characteristics: one where the intervention is more effective, one where the control is more effective, and an optional third where both are equally effective. It includes multiple moderators simultaneously without predefined interactions, detecting higher-order interactions, and represents results as an easy-to-interpret binary tree (Dusseldorp et al., 2016b). Outcome expectations, adherence, and stressful life events will be tested as predictors of treatment response. Furthermore, predictors of adherence, such as demographic variables, symptom severity, and stressful life events, will be investigated.

Light exposure, circadian shift, variability in sleep patterns, pre-sleep arousal, and dysfunctional beliefs and attitudes about sleep will be evaluated as potential mediators of the intervention effect on insomnia severity. The mediators are measured at three time points (T0, T1, and T2), allowing to examine whether treatment-induced changes in mediating variables at T1 predict subsequent changes in outcome at T2. Mediation analysis will be conducted by using multilevel structural equation modeling in R (Preacher et al., 2010), with insomnia severity as dependent variable (Y), group allocation as independent variable (X), and the potential mediator variables (M). All mediators will be investigated separately first and significant mediators will be included in a combined model.

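### Serious illness, and serious accidents outside three listed types, are collected after randomisation in both arms but used only as a covariate or predictor, so the by-arm harms comparison leaves them out

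*Protocol article*

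**What the plan says.** The harms provisions are in section 2.6.3.4 (Adverse events). The timing is "Adverse events will be examined at T1, T2, and T3", and the content is "asking about 1) falling accidents, 2) traffic accidents, or 3) any other accidents related to fatigue or sleepiness", together with the consequences. A second component follows: "Clinical symptom deterioration will also be reported based on the reliability change index".

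The section just before it, 2.6.3.3 (Stressful life events), asks about "life-threatening or serious accident/ illness, death of someone close, physical/sexual violence or abuse or other incidents, at all time-points". The reason given is "Stressful life events can have an impact on sleep and will therefore be examined as a possible covariate".

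Section 2.8.1 (Effectiveness analyses) repeats the covariate role and ties it to imbalance at baseline. Section 2.8.2 (Mediation and moderation analyses) adds another use: "Outcome expectations, adherence, and stressful life events will be tested as predictors of treatment response". Section 1.1 (Aims and hypotheses) states the same predictor role.

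Section 2.4.1 (Coaching) has e-coaches pass adverse events and crises to their supervisor. Sections 2.1 and 2.5 say that the control arm has no e-coach. Section 2.3 says that participants and coaches cannot be blinded.

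**The concern.** A serious accident or illness after randomisation is a candidate harm whatever its cause, and a randomised comparison is the natural way to judge whether treatment contributed. The trial holds the relevant answers from both arms, collected in the same way. The article files them under a heading that treats them as background disturbance to sleep, and nothing links them to the harms section.

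The third accident type raises a separate problem. An accident that is neither a fall nor a traffic accident counts only if it is related to fatigue or sleepiness. The answer is self-reported and the participant knows the allocation. Only one arm works through a module that restricts time in bed (Table 1, module 2) and gets weekly coach feedback. Readiness to link an accident to fatigue may therefore differ between arms even if accident risk does not.

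At stake is the completeness of the safety statement. A summary based on section 2.6.3.4 alone could miss events held in the same database. The primary efficacy analysis is not affected.

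**Working it through.** No arithmetic applies: the article states no harms rate, and the point concerns which event is recorded under which heading. The check sorts post-randomisation events by the article's own definitions. I read the fatigue qualifier as attaching to the third accident type only.

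| Event after randomisation | Adverse-event question (2.6.3.4) | Life-events question (2.6.3.3) | Stated use |
|---|---|---|---|
| Serious fall | Yes, with consequences | Yes | Harms; covariate or predictor |
| Serious traffic accident | Yes, with consequences | Yes | Harms; covariate or predictor |
| Other serious accident, linked to fatigue | Yes, with consequences | Yes | Harms; covariate or predictor |
| Other serious accident, not linked to fatigue | No | Yes | Covariate or predictor only |
| Serious illness | No | Yes | Covariate or predictor only |
| Symptom deterioration | Reported separately, by reliable change index | Not applicable | Harms |

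**Step 1: is the life-events question asked after randomisation?** Its wording covers all time-points, and section 2.6 places T1, T2 and T3 at 3, 6 and 18 weeks after randomisation. Rows four and five are therefore collected while treatment effects are possible.

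**Step 2: does any other section send those answers to harms?** Stressful life events appear in sections 1.1, 2.6.3.3, 2.8.1 and 2.8.2. The roles given are covariate, predictor of treatment response and predictor of adherence. No harms use is stated.

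**Step 3: does another route capture rows four and five?** The e-coach route in section 2.4.1 could, but it exists in one arm only. Reports from it have no control-arm counterpart and cannot support a comparison.

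**Step 4: what separates rows three and four?** Only the link to fatigue, in a self-reported answer from an unblinded participant. With equal accident risk in both arms, different readiness to make that link would give different counts. The article does not allow the difference to be sized.

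**The case against.** The strongest reply is that this article condenses a full protocol approved by an ethics committee. Definitions of serious adverse events, reporting routes and the handling of unsolicited events usually sit in that document, and their absence here proves nothing. That stands for definitions and reporting routes. It does not dispose of the point, because the article itself states what the adverse-event question asks and what the life-events answers are for. If the full document links the two, one sentence here settles the matter.

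A second reply is that targeted accident questions are reasonable for an online sleep programme, and that falls, traffic accidents and sleepiness-related accidents are the harms most plausibly tied to restricted time in bed. That is fair, and is why the questions should stay. It is no reason to leave answers already in hand out of the table.

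Three stronger readings are tempting and are not supported:

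- **That the most serious events are omitted.** Serious falls and traffic accidents are captured with their consequences whatever the cause, and symptom deterioration is reported. Nothing shows that the events left out are the gravest.
- **That the attribution filter hides harm in the intervention arm.** If students taught sleep restriction blame fatigue more readily, the filter would overstate harm in that arm. The documents do not fix the direction.
- **That the effectiveness model will adjust for post-randomisation life events.** Collection at all time-points might suggest it, but section 2.8.1 ties covariates to differences at baseline.

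**Conclusion.** The point holds in a limited form. As the article is written, two kinds of event recorded in both arms after randomisation stay out of the harms comparison: serious illness, and serious accidents that are neither falls nor traffic accidents and are not linked to fatigue. The one open-ended accident item is also filtered by the attribution of unblinded participants. The e-coach route does not repair either gap, because it exists in one arm only.

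The size is unknown: the article gives no rates for these events, and any count would be invented. The conclusion rests on two assumptions: that the fatigue qualifier applies to the third accident type alone, and that the stated uses of the life-events answers are complete as far as harms are concerned. It does not depend on how the full protocol defines a serious adverse event. The change is worth making because it is nearly free and makes the safety comparison more complete.

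**What to change.** 1. In section 2.6.3.4, state that the T1 to T3 answers on serious accident or illness from section 2.6.3.3 will be tabulated by arm, next to the accident items and symptom deterioration. Include only answers that refer to the period since randomisation, and say how that is established, since the article gives no recall window.
2. Label these as participant-reported serious events. They should not automatically be called serious adverse events, because the article describes no check of seriousness.
3. Where the questionnaire can still be changed, ask about any accident first and its perceived relation to fatigue or sleepiness second. Compare the arms on all accidents, and show attribution as a secondary breakdown.

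Items 1 and 2 need only wording and use data already collected. Item 3 splits one question. Recruitment began in November 2023 and was planned to end in July 2024, so the split may no longer be practical; items 1 and 2 stand without it. The cost is a longer harms table that will include some events unrelated to treatment.
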